# SAVER: sodium valproate for the epigenetic reprogramming of high-risk oral epithelial dysplasia—a phase II randomised control trial study protocol

**DOI:** 10.1186/s13063-021-05373-8

**Published:** 2021-07-05

**Keywords:** Oral epithelial dysplasia, Sodium valproate, Epigenetic reprogramming, Drug repurposing, Randomised controlled trial, Chemoprevention

## Abstract

**Background:**

Sodium valproate (VPA) has been associated with a reduced risk of head and neck cancer development. The potential protective mechanism of action is believed to be via inhibition of histone deacetylase and subsequent epigenetic reprogramming. SAVER is a phase IIb open-label, randomised control trial of VPA as a chemopreventive agent in patients with high-risk oral epithelial dysplasia (OED). The aim of the trial is to gather preliminary evidence of the clinical and biological effects of VPA upon OED and assess the feasibility and acceptability of such a trial, with a view to inform a future definitive phase III study.

**Methods:**

One hundred and ten patients with high-risk OED will be recruited from up to 10 secondary care sites in the UK and randomised into either VPA or observation only for 4 months. Women of childbearing potential will be excluded due to the teratogenic properties of VPA. Tissue and blood samples will be collected prior to randomisation and on the last day of the intervention/observation-only period (end of 4 months). Clinical measurement and additional safety bloods will be taken at multiple time points during the trial. The primary outcome will be a composite, surrogate endpoint of change in lesion size, change in grade of dysplasia and change in LOH profile at 8 key microsatellite regions. Feasibility outcomes will include recruitment targets, compliance with the study protocol and adverse effects. A qualitative sub-study will explore patient experience and perception of the trial.

**Discussion:**

The current management options for patients with high-risk OED are limited and mostly include surgical resection and clinical surveillance. However, there remains little evidence whether surgery can effectively lead to a notable reduction in the risk of oral cancer development. Similarly, surveillance is associated with concerns regarding delayed diagnosis of OED progressing to malignancy. The SAVER trial provides an opportunity to investigate the effects of a repurposed, inexpensive and well-tolerated medication as a potential chemopreventive strategy for patients with high-risk OED. The clinical and biological findings of SAVER will inform the appropriateness, design and feasibility of a definitive phase III trial.

**Trial registration:**

The trial is registered with the European Clinical Trials Database (Eudra-CT 2018-000197-30). (http://www.isrctn.com/ISRCTN12448611). The trial was prospectively registered on 24/04/2018.

**Supplementary Information:**

The online version contains supplementary material available at 10.1186/s13063-021-05373-8.

## Background

The incidence of oral squamous cell carcinoma (OSCC) has been increasing for several decades and is predicted to rise 33% by 2035 [1]. The disease results in notably high rates of mortality and morbidity, with 50–60% 5-year survival [2]. Most oral cancers are preceded by long-standing clinical changes of the oral mucosa, mainly white (leukoplakia) and red (erythroplakia) patches, with progression from normal epithelium to invasive OSCC occurring through sequential stages of histological intra-epithelial changes including mild, moderate, and severe dysplasia. A recent systematic review suggests that OED is associated with oral cancer development in 12.1% of cases, with severe OED showing higher rates of progression compared to mild and moderate dysplasia (24.1% vs 10.3%) [3]. Management of OED should aim at reducing the risk of oral cancer development; however, there remains little convincing evidence that this can be achieved with any of the treatment strategies currently adopted in clinical practice [3–5]. OED is typically managed through surveillance or surgical resection [4]; however, neither have strong evidence to support their use nor address the underlying pathogenesis. Surveillance is associated with concerns regarding delayed diagnosis of OED progressing to OSCC [2]. Surgery is not always possible for all lesions or all patients, and recurrence rates for premalignant lesions range from 4 to 30% [6–9]. Also, localised therapies fail to treat the wider mucosal field, often encompassing the entire upper aerodigestive tract, and therefore do not address the risk of multifocal synchronous or metachronous dysplastic lesions. Accordingly, there is an urgent unmet need to develop well-designed clinical trials of novel interventions that, especially in high-risk OED, could effectively reduce the risk of progression to malignancy.

This paper presents the protocol for the SAVER trial, a multi-site, phase IIb, open-label, randomised control trial of VPA in high-risk OED. This trial offers treatment to patients with high-risk lesions who may otherwise have no other option for active treatment and addresses the need for further research in the area of chemoprevention treatment in OED [10]. This protocol report adheres to SPIRIT guidance (Standard Protocol Items: Recommendations for Interventional Trials) [11].

### Evidence supporting the use of sodium valproate as a chemopreventive agent for head and neck cancer

The Kang study is a cohort study of approximately 440,000 patients in the US Veterans’ Affairs System, with long-term psychiatric or neurological diagnoses and at increased risk of smoking-related cancers; 26,000 had been taking VPA for more than one year [12]. There was a lower incidence of head and neck malignancy in the group taking VPA, with a 32% protective effect reported (HR 0.68, 95% CI 0.50–0.93). The reduction in risk was maintained in a multivariate analysis for age, sex, race, past vs current smoking, psychiatric or neurological disease, chronic obstructive pulmonary disease and alcohol and substance use (HR 0.66, 95% CI 0.48–0.92). The weight of this observation is reinforced by dose effect, with both the length of treatment and dose of VPA correlating with a further reduction of risk. The most plausible mechanism of reduction of cancer risk is through the epigenetic reprogramming effects of VPA through histone deacetylase (HDAC) inhibition.

### Rationale for the SAVER trial

The unmet need for an effective treatment to prevent progression of OED to oral cancer, the risk-reduction effect demonstrated in the Kang study and the underlying plausible epigenetic mechanisms underpin the need for a clinical trial using VPA as an HDAC inhibitor in the chemoprevention of oral cancer in individuals with high-risk OED. HDACis are an emerging class of drugs that have shown promise as anticancer agents when used alone or in combination with conventional therapies. HDACi and VPA have been comprehensively reviewed in their role in combination therapies, with either cytotoxic chemotherapy or targeted agents, in haematological malignancy or recurrent/metastatic solid tumours [13, 14]. There is good evidence for clinical benefit of epigenetic therapy in haematological pre-malignancies, such as myelodysplastic syndromes [15]. In contrast, the rationale for HDACi monotherapy in the setting of chemoprevention for oral lesions presents a differing opportunity and there is a paucity of data. There is no in vivo data related to HDACi in oral carcinogenesis; however, there is in vitro evidence of the effect of HDACi on growth inhibition and mediation of apoptosis of OSCC cell lines [16–18]. There is also evidence of growth suppression of xenograft tumours in nude mice [19].

Before embarking in a long and expensive phase III trial, we suggest that preparatory research is needed in order to (i) inform important aspects of the trial design such as feasibility and outcome measures and (ii) identify a preliminary signal of clinical efficacy linked to reasonable biological mechanisms. We have therefore designed a phase IIb trial so to gather data on such preliminary evidence of effect, explore outcome measures and assess the feasibility and acceptability of the trial in this population.

It is expected that the clinical, mechanistic and feasibility data of SAVER will inform the decision for a future larger phase III trial with robust cancer (cancer development) endpoints, necessitating much larger cohorts and longer follow-up.

## Methods and analysis

### Study design and objectives

The SAVER trial is a phase IIb multicentre, open-label, randomised control trial of VPA vs observation only in patients with high-risk OED (see Table 1). The aim of this trial is to investigate the effects of VPA as an epigenetic chemopreventive therapy in high-risk OED. The primary objective is to determine: clinical activity of sodium valproate in high-risk OED, using a composite surrogate endpoint of change in the size of clinical lesion, changes in loss of heterozygosity profile and change in grade of dysplasia (see the ‘Outcome measures’ section). The key secondary objectives are to determine, in subjects with high-risk OED: the mechanism of action of VPA, associated toxicity, overall survival, development of any cancer and the feasibility of conducting such research in the UK National Health Service.

**Table 1 Tab1:** Definition of a high-risk lesion

Definition of a high-risk lesion:	
The index lesion is deemed at high risk of malignant transformation (i.e. estimated >20% over 5 years) if:	
a. Diagnosed as severe OED (WHO grade) or;	
b. Diagnosed as mild or moderate OED (WHO grade), with at least one additional high-risk feature(s) from the list below:	
i. Patient is a non-smoker (less than 100 cigarettes or equivalent over whole lifetime)	
ii. Lesion size > 200 mm^2^	
iii. Lateral tongue site	
iv. Mucosal speckling or heterogeneous appearance	
v. Patient had an excised OSCC during previous 5 years (but not within previous 6 months).	

### Recruiting centres

SAVER is coordinated by the Liverpool Clinical Trials Centre (LCTC) and is sponsored by the University of Liverpool.

### Study population and inclusion criteria

Patients will be recruited via Oral Medicine, Oral and Maxillofacial Surgery outpatient and Oral Dysplasia Multidisciplinary clinics at the study sites. Eligible patients will have a lesion that is accessible, measurable (at least 100 mm^2^), amenable to clinical photography and located in the oral cavity or oropharynx or on the lip. As part of the screening process for SAVER, all patients will require an incisional biopsy of the index lesion to confirm eligibility; only patients with a biopsy confirming a histopathological diagnosis of OED, considered to be at high risk of transforming to oral cancer, will be included. The definition of a high-risk lesion can be found in Table 1.

There must be a treatment plan for either surgical resection or close monitoring (clinical and photographic follow-up). The patient must be fully informed, have received Patient Information Sheet (PIS) and considered this during a ‘cooling-off’ period, be competent to consent, age ≥ 18 and able to comply with minimum attendance requirements. Exclusion criteria can be found in Table 2.

**Table 2 Tab2:** Exclusion criteria for the SAVER trial

**Exclusion criteria**	
1. Synchronous or metachronous OSCC (i.e. at time of screening or within 6 months)	
2. Active malignancy outside head and neck region (with exception of non-melanoma skin cancer)	
3. Currently positive for COVID-19 (patients who have recovered from COVID-19 are NOT excluded)	
4. OSCC susceptible conditions e.g. Fanconi anaemia, Blooms syndrome, ataxia-telangectasia and Li-Fraumeni syndrome	
5. Clinical and/or histopathological diagnosis of oral submucous fibrosis	
6. Immunosuppression. However, low dose i.e. < 10mg/day prednisolone, or equivalent steroid, (as per BNF conversion table), are not considered an exclusion.	
7. Chronic previous or current use of sodium valproate	
8. Diagnosed epilepsy that has chronic previous or current use of *any* antiepileptic therapy	
9. Obesity (body mass index ≥ 30)	
10. Known relative or absolute contraindications to Sodium Valproate (as listed in British National Formulary), and specifically:	
a. Acute porphyria	
b. Known or suspected mitochondrial disorders	
c. Personal or family history of severe hepatic dysfunction, current hepatic dysfunction (as evidenced by LFTs outwith reference range and prolonged prothrombin time)	
d. Past history or current pancreatitis	
e. Women with child-bearing potential. A woman is considered of childbearing potential (WOCBP), i.e. fertile, following menarche and until becoming post-menopausal unless permanently sterile. Permanent sterilisation methods include hysterectomy, bilateral salpingectomy, and bilateral oophorectomy.	
f. Potential drug interactions (particularly antipsychotic and anticonvulsant medications, MAO inhibitors, antidepressants, benzodiazepines), specifically patients taking phenobarbital, primodone, carbopenem antibiotics (imipenem, panipenem, meropenem), cimetidine, erythromycin, lamotrigine, olanzapine, pivmecillinam, sodium oxybate, zidovudine, carbamazepine, phenytoin, rifampicin, high dose salicylates including aspirin > 75 mg daily (patients taking low dose aspirin 75 mg daily are eligible).	
g. Patients with suicidal ideation and behaviour should be excluded from the trial. Patients should also be monitored for signs of suicidal ideation and behaviours and appropriate treatment should be considered.	
h. Patients with known or suspected mitochondrial disease, systemic lupus erythematosus or hyperammonaemia	

Details of the management of patients being randomised or having surgery within the SAVER trial during the COVID-19 pandemic can be found in Additional file 1.

### Randomisation

Randomisation will be completed centrally by the LCTC via a password-protected web-based tool called the Treatment Allocation Randomisation System (TARDIS). All patients will be allocated a unique randomisation number. Randomisation must be carried out within 90 days of the research biopsy report and commencement of trial treatment within 30 days of the date of randomisation. Patients will be randomised between VPA (arm A) and observation only (arm B) in the ratio 2:1, with site used as a stratification factor.

#### Arm A

VPA (Epilim) will initially be taken orally for 14 days at a dose of 500 mg once daily. From day 15 until 4 calendar months after day 1, VPA will be taken orally continuously at a dose of 500 mg twice daily. A 5-mm punch biopsy will be taken at the 4-month time point.

#### Arm B

Patients in the control group will not receive any trial medication. They will be monitored at the same intervals as patients in Arm A (2, 4 and 6 months from baseline) and will subject to the same blood monitoring schedule. A 5-mm punch biopsy will be taken at the 4-month time point, as for Arm A.

### Schedule of events

Figure 1 shows the flow of patients through the trial and the SPIRIT figure (Fig. 2) gives details of the procedures required at each trial time-point. A screening biopsy (incisional biopsy) is taken to confirm eligibility, prior to randomisation. Patients are randomised to one of two arms (sodium valproate or observation only), for 4 months. A repeat biopsy is taken on the final day of trial medication at the 4-month time-point for both groups. A clinical photograph and bloods are also taken at this visit for both groups. In total the patient is examined five times during the trial period for signs of lesion progression.

**Fig. 1 Fig1:**
[figure not shown]
Patient activity through the SAVER trial

**Fig. 2 Fig2:**
[figure not shown]
Spirit figure

Adverse events are monitored through the Liverpool Adverse Events Reporting Questionnaire at 3 points during the trial and at any unscheduled trial visits. All patients will have a full blood count, clotting screen and LFTs performed as outlined in the schedule, to assess for potential haematological and hepatic toxicities and clotting aberrations.

### Clinical progression during the trial

If a lesion is seen to have progressed and the clinician is concerned regarding malignant transformation, an urgent biopsy is requested and reported through the central pathology unit at Newcastle Hospital. If the diagnosis confirms malignant transformation, the patient ceases study drug (if relevant) is withdrawn from the trial and returns to normal clinical management and follow-up. If histopathology does not show malignant transformation, the patient returns to normal study schedule or normal standard of care.

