### Secondary outcome measure

Secondary endpoints will be assessed including toxicity (measured using Common Terminology Criteria for Adverse Events (CTCAE) v4.03 classification), overall survival and malignancy of the head and neck (or other sites) during the patient’s active trial period and for the total duration of the trial. Feasibility endpoints will be recorded, defined by overall and centre-specific rate of recruitment, compliance with treatment, protocol deviations and drop-out rates.

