### Criteria for discontinuing or modifying allocated interventions

Patients may be withdrawn from treatment for any of the following reasons: Development of an OSCC, unacceptable toxicity, any change in the patient’s medical condition that justifies discontinuation of treatment in the clinician’s opinion and pregnancy.

Treatment may be discontinued for any toxicity with a significant impact on quality of life (generally grade 2 or higher; however, persistent grade 1 adverse events (AEs) may also lead to discontinuation). A 50% dose reduction (500 mg/day) may also be considered for persistent grade 1 toxicities rather than withdrawal from the trial. Patients discontinuing due to toxicity will be followed up and assessed as per protocol. Patients discontinuing treatment for any reason will continue to be followed up unless the patient explicitly withdraws consent for follow-up. If the patient explicitly states their wish not to contribute further data to the study, a withdrawal CRF will be completed. Anonymised data collected up to this point can still be used for study purposes.

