### Adverse events

All adverse events that occur from the point of the patient’s written informed consent are to be reported, even if the patient has not started taking VPA. All adverse events should be reported up to the point of the primary endpoint being established, with the exception of malignant transformation or new head and neck cancer, which should be collected until trial closure. All non-serious adverse events (AE)/adverse reactions (AR), whether expected or not, will be recorded in the relevant page of the CRF. Serious adverse reactions (SARs), serious adverse events (SAEs) and suspected unexpected serious adverse reactions (SUSARs) should be reported within 24 h of the local site becoming aware of the event. The SAE form asks for the nature of event, date of onset, severity, corrective therapies given, outcome and causality. The responsible investigator should sign the causality of the event. Additional information should be sent within 5 days if the reaction has not resolved at the time of reporting. The LCTC will notify the MHRA and main Research Ethics Committee (REC) of all SUSARs occurring during the study according to the following timelines; fatal and life-threatening within 7 days of notification and non-life-threatening within 15 days. All investigators will be informed of all SUSARs occurring throughout the study. Local investigators should report any SUSARs and/or SAEs as required by their Local Research Ethics Committee and/or Research and Development Office.

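### The rule that removes patients from the trial at malignant transformation conflicts with the continued follow-up promised elsewhere and, read literally, censors overall survival at the cancer diagnosis

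*Protocol article*

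**What the plan says.** Five parts of the protocol article bear on this.

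- **Clinical progression during the trial.** If an urgent biopsy confirms malignant transformation, "the patient ceases study drug (if relevant) is withdrawn from the trial and returns to normal clinical management and follow-up".
- **Criteria for discontinuing or modifying allocated interventions.** The same kind of event appears as a treatment matter: "Patients may be withdrawn from treatment for any of the following reasons: Development of an OSCC". The section then adds: "Patients discontinuing treatment for any reason will continue to be followed up unless the patient explicitly withdraws consent for follow-up". A withdrawal form is completed for a patient who explicitly wishes to contribute no more data.
- **Study design and objectives** and **Secondary outcome measure.** The key secondary objectives include "overall survival, development of any cancer". The outcome section sets survival and malignancy, in the head and neck or elsewhere, over both the patient's active period and the full length of the trial.
- **Adverse events.** General reporting stops once the primary endpoint has been determined. Two kinds of event are carved out of that cut-off: "with the exception of malignant transformation or new head and neck cancer, which should be collected until trial closure".
- **Statistical analysis.** Analyses other than toxicity follow intention to treat. Time-to-event data are compared by stratified log-rank test, with Cox models if proportional hazards is not violated.

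**The concern.** A site with a newly transformed patient has two instructions. One takes the patient out of the trial. The other takes the patient off treatment and keeps the patient under observation. Both cannot be followed.

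The choice matters for overall survival. If observation ends when cancer is confirmed, each such patient is censored at the point where the risk of death changes. The log-rank test and the Cox model assume that censored patients have the same future risk as those still followed, and that would not hold here. The article's Background puts 5-year survival with oral squamous cell carcinoma at 50–60%. Second cancers in the same patients would be lost too, and intention to treat calls for keeping these patients under observation.

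A related gap is that the exception in the Adverse events section is narrower than the endpoints. It extends collection to closure for transformation and new head and neck cancer, but names neither deaths nor cancers at other sites.

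**Working it through.** **Step 1: the rules side by side**

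| Question | Clinical progression section | Discontinuation section | Endpoint sections |
|---|---|---|---|
| What ends at a confirmed cancer? | Participation in the trial | Treatment | – |
| Follow-up afterwards? | Ordinary clinical follow-up, outside the trial | Trial follow-up, unless consent is withdrawn | Survival and any malignancy needed to the end of the trial |

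The second and third columns agree with each other. The first agrees with neither.

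**Step 2: what would be lost and what would not**

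- The transformation that triggers the rule is not lost. The Total responsiveness score section classes it automatically as disease progression, and it is also a malignancy event.
- Head and neck cancers after the primary endpoint are not lost as a class, because the Adverse events section collects them until closure.
- At risk under the literal rule are the later death, or a second cancer, of a patient who has already transformed.

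**Step 3: how many patients**

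The plan gives no event count for survival or cancer, so there is no figure of its own to reproduce here.

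Inputs:
- N = 110 (Sample size calculation).
- Transformation risk above 20% over 5 years (Table 1). I use 20%, so the central results lean low.
- Accrual over 32 months (Sample size calculation).
- December 2019 to July 2023, about 43 months (Trial Status).
- Assumptions: constant hazard, no losses for other reasons, and uniform accrual. The last ignores the temporary halt to recruitment.

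Hazard: λ = −ln(0.80)/60 = 0.003719 per month (0.0446 per year).

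Expected number transforming within t months: 110 × (1 − exp(−λt)).

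- To month 4: 110 × (1 − exp(−0.01488)) = **1.6**
- To month 6, the last monitoring visit: 110 × (1 − exp(−0.02231)) = **2.4**

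If the rule runs to closure, follow-up ranges evenly from 43 − 32 = 11 to 43 months, with mean 27. Averaging over that range:

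110 × {1 − [exp(−11λ) − exp(−43λ)]/(32λ)} = 110 × {1 − (0.9599 − 0.8522)/0.1190} = **10.5**

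Sensitivity to the 5-year risk. The 12.1% is the overall figure for dysplasia in the Background, treated here as a 5-year risk. The 30% is an assumed upper value.

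| 5-year risk | To month 4 | To month 6 | To closure |
|---|---|---|---|
| 12.1% | 0.9 | 1.4 | 6.2 |
| 20% | 1.6 | 2.4 | 10.5 |
| 30% | 2.6 | 3.9 | 16.2 |

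These are patients whose later observation is at stake, not lost deaths. The article gives no mortality figure for patients who do not transform, so the share of all deaths they would hold cannot be derived.

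**The case against.** The strongest reply is that the article largely answers the question itself. The discontinuation section names oral squamous cell carcinoma, promises follow-up after stopping for any reason, and describes a withdrawal form for patients who say they want to contribute no more data. On that view the conflicting phrase is loose wording, and informative censoring is a risk of literal reading rather than a demonstrated defect. This stands in part: it makes the intended rule fairly clear and lowers the severity. It does not remove the contradiction, because the other section still tells sites to take the patient out of the trial.

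A second reply is that the rule sits among instructions about the study drug and the study schedule, so it most naturally covers patients still on scheduled visits. That favours the smaller counts of 1.6 to 2.4 over the figure of about 10. I accept this as the likelier reading, although the text does not fix the period.

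Two stronger inferences are tempting, and the article supports neither.

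- **That event reporting in general stops at month 4, so that cancers are counted over only four months.** The Adverse events section expressly collects transformation and new head and neck cancer until closure. It governs adverse event reporting, so its silence on deaths and other-site cancers does not show that they go uncollected; the full protocol may provide another route.
- **That adverse event reporting ends on the day of the last dose.** The cut-off is when the primary endpoint is established. The biopsy is taken on the last day of medication, but the endpoint also needs histology, loss-of-heterozygosity results and blinded reading. The visit schedule figure is not available to settle the timing.

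**Conclusion.** The inconsistency is real and should be corrected. The rule on confirmed transformation conflicts with the rule on follow-up after stopping treatment and with endpoints defined over the whole trial. Followed literally, it would censor overall survival informatively and lose second cancers in the patients concerned.

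The size is small on the likelier reading (about 2 of 110 patients) and about 10 if the rule extends to closure. Both rest on a 20% 5-year risk with constant hazard; the second also needs uniform accrual and closure at month 43. A reader might go further and infer that these patients hold most of the deaths, but the article offers no basis for that share.

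Only secondary endpoints are affected. The primary response endpoint already classes transformation as progression, and the sample size rests on the response rate. Severity is moderate to minor.

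**What to change.** Two changes of wording, both about data collection. Neither alters any decision on treatment.

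1. **Clinical progression during the trial.** Reconcile with the discontinuation section on trial status: a patient with confirmed transformation remains in trial follow-up for survival and malignancy unless consent for follow-up is withdrawn.
2. **Adverse events.** Align the exception with the Secondary outcome measure section by naming death from any cause and malignancy at any site as collected until trial closure, in both arms. If the full protocol already collects these by another route, a cross-reference is enough.

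The cost is a protocol amendment and a status check by sites or from records at closure. It is best done early, because follow-up that has been allowed to lapse may be hard to recover.
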